## Abstract

**Background:**

The likelihood of return of spontaneous circulation with conventional advanced life support is known to have an exponential decline and therefore neurological outcome after 20 min in patients with a cardiac arrest is poor. Initiation of venoarterial ExtraCorporeal Membrane Oxygenation (ECMO) during resuscitation might improve outcomes if used in time and in a selected patient category. However, previous studies have failed to significantly reduce the time from cardiac arrest to ECMO flow to less than 60 min. We hypothesize that the initiation of Extracorporeal Cardiopulmonary Resuscitation (ECPR) by a Helicopter Emergency Medical Services System (HEMS) will reduce the low flow time and improve outcomes in refractory Out of Hospital Cardiac Arrest (OHCA) patients.

**Methods:**

The ON-SCENE study will use a non-randomised stepped wedge design to implement ECPR in patients with witnessed OHCA between the ages of 18–50 years old, with an initial presentation of shockable rhythm or pulseless electrical activity with a high suspicion of pulmonary embolism, lasting more than 20, but less than 45 min. Patients will be treated by the ambulance crew and HEMS with prehospital ECPR capabilities and will be compared with treatment by ambulance crew and HEMS without prehospital ECPR capabilities. The primary outcome measure will be survival at hospital discharge. The secondary outcome measure will be good neurological outcome defined as a cerebral performance categories scale score of 1 or 2 at 6 and 12 months.

**Discussion:**

The ON-SCENE study focuses on initiating ECPR at the scene of OHCA using HEMS. The current in-hospital ECPR for OHCA obstacles encompassing low survival rates in refractory arrests, extended low-flow durations during transportation, and the critical time sensitivity of initiating ECPR, which could potentially be addressed through the implementation of the HEMS system. When successful, implementing on-scene ECPR could significantly enhance survival rates and minimize neurological impairment.

**Trial registration:**

Clinicaltyrials.gov under NCT04620070, registration date 3 November 2020.

## Background

Of the patients who survive an Out-of-Hospital-Cardiac-Arrest (OHCA), approximately 90% achieves return of spontaneous circulation (ROSC) within 15 min [1]. In case of refractory arrest, often defined as ROSC not obtained within 20 min, favourable neurological outcome is uncommon (OR 0.03) [1–3]. Currently, patients failing to reach ROSC are either declared deceased on-site or transported to the hospital for further treatment, including potential Extracorporeal Cardiopulmonary Resuscitation (ECPR) eligibility. The application of ECPR is a rapidly growing, and although ECPR could be an effective treatment, its success relies heavily on being initiated in time [4].

Multiple studies have demonstrated that in patients receiving ECPR for refractory OHCA, a cardiopulmonary resuscitation duration of less than 40 min was strongly associated with better survival with minimal neurological impairment [5–8]. Suboptimal thoracic compression during transportation further reduces survival probability, leading to prolonged low-flow times [9], especially if the cardiac arrest occurs far from an ECPR centre (Fig. 1).

**Fig. 1 Fig1:**
[figure not shown]
The 10 ECPR centres with their 30 min radius

Initiating ECPR at the cardiac arrest scene could potentially overcome both problems by reducing the duration of the low-flow state and limiting thoracic compression during transport. Performing ECPR at the scene will enlarge the potential patient pool to include individuals who might not meet the criteria for in-hospital rescue therapy due to the prolonged period of low flow caused by transportation delay. With the use of the Helicopter Emergency Medical Services (HEMS), the geographic range can be extended while maintaining a short low-flow time. This perspective is the cornerstone of the ON-SCENE study.

In the Netherlands, HEMS teams consist of an anaesthesiologist or trauma surgeon, an emergency or ambulance registered nurse, and a pilot. Their primary goal is to provide specialized medical care to trauma and non-trauma patients throughout the country with an arrival at scene after approximately 11 min. Dispatching the HEMS simultaneously with the first responders after OHCA, could potentially shorten time between collaps and initiation of ECMO bloodflow which in turn could significantly improve the chance of survival compared to either conventional resuscitation without ECPR and ECPR initiated in-hospital [10].

We therefore designed and set up the ON-SCENE study to investigate the effect of equipping the HEMS with prehospital ECPR facility on hospital survival. In this HEMS setting, a nationwide coverage for prehospital ECPR in a timely manner would be achieved. The hypothesis of this study is that implementing nationwide on scene ECPR in patients with OHCA results in shorter low-flow time in comparison to regular care, which leads to improved survival rates and less neurological impairment. Despite the increased costs for delivering ECPR on scene, it is likely to be cost-effective.

## Methods

### Trial design

This is a nationwide multicentre, prospective, interventional, non-randomised stepped wedge study that evaluates the effect of prehospital ECPR in patients with witnessed OHCA between the age of 18 and 50 years old versus conventional HEMS care without ECPR. The study started end of 2021 and is scheduled to finish by the end of 2025.

### Eligibility criteria

Patients with a witnessed OHCA between the age of 18 and 50 years old and an initial presentation of ventricular fibrillation/pulseless ventricular tachycardia, as well as pulseless electrical activity with a high suspicion of pulmonary embolism are eligible for inclusion. Detailed inclusion and exclusion criteria are listed in Table 1. The eligibility criteria aim to identify patients with a cardiac arrest that have treatable underlying causes.

**Table 1 Tab1:** Inclusion and exclusion criteria

**Inclusion criteria**	**Exclusion criteria**
Witnessed out of hospital cardiac arrest	ROSC ≤ 20 min
≥ 18 ≤ 50 years (known or estimated)	Expected time from collapse to arrival at an ECPR centre with a direct available ECPR team is less than 30 min.
Initial rhythm of (p)VT /VF or suspected PE	EtCO_2_ et < 1.2 kPa (10 mmHg) during CPR
Refractory cardiac arrest ≥ 20 min ≤ 45 min	No clear ultrasound visualisation of either the femoral artery or the femoral vein.
	**Following initial inclusion, the following patients will be eliminated as soon as the following details are made available**
	Active malignancy
	Cerebral vascular accident < 6 weeks
	Patients with a “do not resuscitate” order, which was not known at time of the arrest

*(p)VT* (pulseless) Ventricular Tachycardia, *VF* Ventricular Fibrillation, *PE* Pulmonary Embolism, *ROSC* Return of Spontaneous Circulation, *ECPR* Extracorporeal Cardiopulmonary Resuscitation, *CPR* Cardiopulmonary Resuscitation, *kPa* Kilopascal

Witnessed arrest is defined as patients who have been last seen well less than 5 min before or show signs of life, meaning extremity movements, normal pupillary reflexes, or gasping during CPR. Whenever the exact age is unknown at the time of care, it is estimated by HEMS. If the patient later on found to be outside the inclusion range of age after cannulation, they will not be excluded.

The time of start of arrest to expected time of arrival at the hospital should be longer that 30 min to be eligible to prehospital ECPR. Furthermore, it should be assumed that the ECPR team would be ready on the ER when the patient arrives. If this is not expected, patient will then receive prehospital ECPR. Only very few patients are so close to the hospital that start of arrest to expected time of arrival hospital is less than 30 min.

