### Allocation of patient

There are four HEMS stations serving the Netherlands, situated in Groningen, Rotterdam, Amsterdam, and Nijmegen (Fig. 2) which cover the majority of the country. Before this study, HEMS crews are not routinely involved in adult OHCA cases. In this study, HEMS will be dispatched simultaneously with the emergency medical services to every witnessed OHCA involving patients suspected to be between the ages of 18 and 50 years. As ECPR will not be offered in a regional manner (as it is typical nowadays) but on a national level, we were cautious not to overwhelm the system. To limit the number of ECPR cases, we exclude patients older than 50 years. A computer-aided system will assist the dispatcher in the central dispatch centre to determining patient eligibility. In the intervention group, the HEMS will be equipped with ECPR equipment. In the control group, HEMS will also be deployed, but without ECPR equipment. This is done to prevent a second treatment effect in the ECPR group, being the assistance of the HEMS team on scene.

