### Treatment in the intervention group, prehospital ECPR

In the intervention group, HEMS personnel will initiate ECMO cannulation after 20 min of refractory cardiac arrest. The decision to proceed with the cannulation is made solely by the HEMS physician on the basis of the available information regarding the inclusion and exclusion criteria. Since the time it takes for ECMO initiation significantly impacts outcomes, HEMS will collect both the arrival time at the patient location and the time of ECMO flow.

Vascular access will be ascertained through an ultrasound guided puncture of the femoral artery and vein. Insertions of an 25 French venous cannula and a 17 French arterial cannula is performed followed through a Seldinger procedure using an Amplatz Super Stiff™ (with J-tip) guidewire. If they estimated weight is below 50 kg, an 21 French venous and 15 French arterial cannula is inserted(Getinge, Germany). The ECMO machine will then be connected to the cannulas to restore blood flow mechanically, after which chest compressions can be stopped. Target ECMO flow will be between 3 and 4 L per minute and a mean arterial pressure (MAP) of at least 75 mmHg measured with an invasive femoral arterial line placed in the other groin. Arterial blood pressure will be measured using a disposable Compass pressure device (Centurion Medical Products, USA). The ECMO oxygen fraction will initially be set at 0.6 with a standard sweepflow of 2L/min. Ventilation will be maintained at a tidal volume of 4 ml /kg of ideal bodyweight and a respiratory rate of 6 per minute to prevent a rapid decrease in PaCO2. Saturation levels will be measured on the right hand to detect a possible harlequin syndrome. The cannulas will be fixated, and the patient will be transported by ambulance to the nearest hospital providing ECMO care. Standard post-resuscitation care will be provided in the hospital.

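### Femoral visualisation failure is a study exclusion that only the ECPR arm is shown to test, and included patients are later eliminated; neither fits the intention-to-treat label

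*Protocol article*

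**What the plan says.** Table 1 (Protocol article, Eligibility criteria) is a single list for the whole study. Among the exclusions is "No clear ultrasound visualisation of either the femoral artery or the femoral vein". A second block removes patients who have already entered: "Following initial inclusion, the following patients will be eliminated as soon as the following details are made available". It names active malignancy, a cerebrovascular accident within six weeks, and a DNR order not known at the time of the arrest.

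The section on treatment in the intervention group is the only place where ultrasound is used: "Vascular access will be ascertained through an ultrasound guided puncture of the femoral artery and vein". The same section says "The decision to proceed with the cannulation is made solely by the HEMS physician on the basis of the available information" regarding the eligibility criteria. Of the other arm, Allocation of patient says "In the control group, HEMS will also be deployed, but without ECPR equipment". The control-treatment section describes no femoral check and no matching decision point.

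Under Ethical considerations, screening takes place after the HEMS team arrives. Under Statistical analysis, the primary comparison of hospital survival is an unadjusted chi-square test labelled intention to treat.

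On age, Table 1 accepts 18 to 50 years, known or estimated, and the text adds: "If the patient later on found to be outside the inclusion range of age after cannulation, they will not be excluded".

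**The concern.** The question under Background is what equipping HEMS with prehospital ECPR does to survival. A patient whom an equipped crew cannot cannulate because the vessels cannot be seen is part of that answer. Table 1 instead takes this patient out of the study. The control counterpart, whom nobody is described as scanning, would stay in.

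The late eliminations raise a related problem. They are pre-arrest facts and nominally apply to both arms, but they act only when someone learns of them. Cannulated patients are all taken to an ECMO hospital, where history tends to emerge. The sample-size section assumes that 70% of controls are not transported to an ECPR facility during the arrest. If discovery differs, removal differs.

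If the patients removed have a poor prognosis and come mainly from the ECPR arm, survival there rises without any treatment effect. The trial is non-randomised, and crews know their arm when they screen. The planned GEE model adjusts for covariates of patients who remain; it cannot restore those removed.

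**Working it through.** **Inputs from the document (Sample size).** ECPR survival 35%. Control: 30% transported for in-hospital ECPR with 26% survival, 70% not transported with 16% survival. 175 per arm, 90% power, alpha 0.05 (two-sided assumed).

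**The plan's own figure.** Control rate = 0.30 × 0.26 + 0.70 × 0.16 = 0.19. For 35% against 19% at 90% power, the standard two-proportion formula gives 160 per arm, or 172 with continuity correction. If one-seventh of ECPR patients (assumed) fall in the 30% learning phase, the uncorrected formula gives 174. So 175 is consistent with the stated inputs, although the trial's simulation is not shown. Power at 175 per arm for 35% against 19% is 92.4%, ignoring clustering and the learning phase.

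**Spurious gain under no effect.** Let both arms have 19% survival. Remove a share f from the ECPR arm only, with survival s among those removed. Both f and s are assumptions; the documents give neither. ECPR survival becomes

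p = (0.19 − f·s) / (1 − f).

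Example: f = 0.15, s = 0 gives 0.19 / 0.85 = 0.2235, a gain of 3.35 points. The rejection rate is that of the two-sided uncorrected chi-square test by normal approximation, with 175 analysed per arm.

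| f | s | ECPR survival | Spurious gain (points) | Rejection rate |
|---|---|---|---|---|
| 5% | 5% | 19.7% | 0.7 | 5.4% |
| 5% | 0% | 20.0% | 1.0 | 5.6% |
| 10% | 5% | 20.6% | 1.6 | 6.5% |
| 10% | 0% | 21.1% | 2.1 | 7.8% |
| 15% | 5% | 21.5% | 2.5 | 8.9% |
| 15% | 0% | 22.4% | 3.4 | 12.1% |
| any | 19% | 19.0% | 0 | 5.0% |

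Exact enumeration of the same test agrees within 0.1 percentage point. With continuity correction the worst corner is 9.6%, against 3.6% when there is no bias. The planned difference is 35 − 19 = 16 points, so 3.4 points is about a fifth of it.

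**Power once these patients are kept.** Let a share f of the ECPR arm be uncannulated and survive at 19%: p = (1 − f) × 0.35 + f × 0.19. Controls stay at 19%.

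| f | ECPR survival | Power, 175 per arm | n per arm for 90% |
|---|---|---|---|
| 0 | 35.0% | 92.4% | 160 |
| 5% | 34.2% | 89.9% | 176 |
| 10% | 33.4% | 86.8% | 194 |
| 20% | 31.8% | 78.8% | 241 |

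The article also gives a total of 390, which is not 2 × 175 = 350, and does not explain the difference. If 195 per arm were analysed, the powers would be 94.8, 92.8, 90.2 and 83.0%.

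**The case against.** Much can be said on the other side. That controls are not screened by ultrasound is an inference: the article says their crews lack ECPR equipment and does not mention ultrasound, and the full protocol may say how Table 1 is applied to controls. Nothing shows that poor visualisation marks a poor prognosis. The late eliminations are pre-arrest facts, nominally the same for both arms. The 70% of controls not taken to an ECPR facility during arrest are not all dead on scene, since 16% of them are assumed to survive to discharge. History could also be sought for those who die there. These points stand, and they limit what can be said about size. They do not remove the conflict between the stated exclusions and the intention-to-treat label.

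A reader might infer two further faults that the document does not support.

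- **Age.** The sentence on age could be read as protecting misjudged patients in the ECPR arm only. Table 1 accepts estimated age for the whole study, so a control judged in range also qualifies. The sentence retains patients, which is in the spirit of intention to treat. Some controls may be cannulated in hospital, and keeping older patients would more likely work against ECPR.
- **Time window.** The abstract's phrase "lasting more than 20, but less than 45 min" could be read as total arrest duration, which would drop controls who receive in-hospital ECPR late. The control-treatment section, the sample-size assumptions and the planned subgroup analysis all keep such controls. The criterion can be assessed in both arms.

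**Conclusion.** The point holds for the femoral-visualisation exclusion and, in part, for elimination after inclusion. The first ties membership of the study to a step described only for the intervention. The second lets membership depend on later information whose equal ascertainment is not secured. Both contradict an intention-to-treat primary analysis.

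The direction is plausibly in favour of ECPR but is not established. It requires that removals fall mainly in the ECPR arm and that those removed do worse than average. Under the assumed 5–15% removal with 0–5% survival, the spurious gain is 0.7–3.4 points and the rejection rate about 5.4–12.1%. It is nil if those removed survive at 19%. This is an illustration, not an estimate, and it does not show that the trial's result will be wrong.

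**What to change.** Leave clinical practice as it is and change the definition of the primary analysis set:

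- Admit patients on criteria that can be assessed in the same way in both arms at a common time point, and keep each in the arm set by the station's status at dispatch.
- Count failed femoral visualisation as an untreated patient of the intervention arm.
- Use malignancy, recent stroke and DNR order only in a sensitivity analysis, with history sought equally in both arms and removals reported by arm.
- State that patients estimated to be in the age range are kept in both arms, irrespective of cannulation.

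This needs new wording and retention of data on patients already excluded or eliminated under these rules. The cost is power. If 5, 10 or 20% of the ECPR arm is not cannulated and survives at 19%, power at 175 per arm falls from about 92% to about 90, 87 or 79%; it falls further if those patients do worse. The stated power should be restated for the revised analysis set, ideally by rerunning the plan's own simulation.

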### Allocation of patient

There are four HEMS stations serving the Netherlands, situated in Groningen, Rotterdam, Amsterdam, and Nijmegen (Fig. 2) which cover the majority of the country. Before this study, HEMS crews are not routinely involved in adult OHCA cases. In this study, HEMS will be dispatched simultaneously with the emergency medical services to every witnessed OHCA involving patients suspected to be between the ages of 18 and 50 years. As ECPR will not be offered in a regional manner (as it is typical nowadays) but on a national level, we were cautious not to overwhelm the system. To limit the number of ECPR cases, we exclude patients older than 50 years. A computer-aided system will assist the dispatcher in the central dispatch centre to determining patient eligibility. In the intervention group, the HEMS will be equipped with ECPR equipment. In the control group, HEMS will also be deployed, but without ECPR equipment. This is done to prevent a second treatment effect in the ECPR group, being the assistance of the HEMS team on scene.

**Fig. 2 Fig2:**
[figure not shown]
HEMS Region with their 20 min geographic radius. HEMS: Helicopter Emergency Medical Services

After start of the study some large dispatch centres still seemed not ready to dispatch the HEMS because of legal uncertainties. Therefore, just after start of the study, an amendation to extend the study period was filed. To prevent protocol violation, dispatch centres who weren’t ready at the start of the study were excluded until being completely ready to comply with the study protocol.

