### Training of HEMS personnel

Training is key for all high-stakes procedures, especially under time constraints. Given that the capacity to train all HEMS teams at the same time is limited, a stepped-wedge design was chosen (Fig. 3) [11, 12].

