**Fig. 3 Fig3:**
[figure not shown]
Schematic timetable of the stepped-wedge study design. ECPR experienced personnel and non-ECPR experienced personnel). HEMS: Helicopter Emergency Medical Service. CCPR: HEMS operating without ECMO: Conventional CardioPuImonary Resuscitation. ECPR: HEMS operating with ECMO: Extra-Corporeal CardioPulmonary Resuscitation Training: Timing training of HEMS personnel

This design also prevents cross-over to the intervention arm in young patients who fail to achieve return of spontaneous circulation, thereby improving the study’s quality.

To train the HEMS personnel, a mobile high-fidelity ECMO training simulation centre that offers team-based training in ECPR cannulation and management will be used. This training program is used for years to train thoracic intensivist for achieving a 24/7 in-hospital ECPR service.

Each HEMS crew member will undergo a comprehensive training program led by a minimum of three trainers for every six members, consisting of theoretical and practical elements. The training will include a-4 h E-learning sessions followed by a 6-h plenary sessions. The practical component of the training will include a 2 day training period involving hands-on experience, with each crew member performing at least 10 cannulations on a specially designed mannequin. These cannulations will be executed in high-fidelity simulations, gradually increasing in complexity and incorporating challenging scenarios that simulate uncomfortable positions and environments mirroring real-life situations. The initial training is signed off by a mannequin cannulation in a challenging condition, without errors and in a timely manner. After completion, HEMS stations will be equipped with ECPR facilities. Continuous training will follow for 6 months on a weekly basis, then ongoing sessions every 3 months. Beyond cannulation, training will encompass ECMO management and troubleshooting, facilitated by experienced perfusionists and ECMO intensivists, using real in-hospital patient to enhance skills and maintain proficiency.

To provide ongoing support to HEMS crew during and after cannulation, a 24-h telemedicine system is established. Immediately after cannulation and before transport, a mandatory live videocall is made with ECMO physicians and perfusionists.

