### Statistical analysis

#### Primary and secondary

The primary outcome measure, hospital survival, will be analysed by descriptive statistics per group and percentage of total. Differences in hospital survival between groups (intervention and control group) will be tested using univariate analysis (intention to treat) by means of a Chi-square test.

As a result of the cluster effect, the primary analysis using unadjusted Chi-square test might be biased. To asses for this and other cofounders a secondary, multivariable analysis will be performed using Generalized Estimating Equations (GEE). Survival will be a dependent variable, prehospital ECPR will be included as covariate. No prehospital ECPR will be the reference category. Baseline and EMS/dispatch related variables that may potentially confound the association between prehospital ECPR and outcome will be included in this model as covariate. Known potential confounders include age, gender, time to ambulance arrival on scene, low-flow time, known medical cardiovascular conditions having an increased risk of sudden cardiac arrest. If these variables produce a *p*-value < 0.2 in a univariate comparison between the two groups, they will be included in the regression model.

Secondary outcome like survival with good neurological outcome (defined as CPC 1–2) at 6 and 12 months will be analysed using a logistic mixed regression analysis for between the two groups.

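### Late-joining large dispatch centres are likely under-represented among controls, and the unadjusted primary test cannot separate that shift in catchment from the effect of prehospital ECPR

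*Protocol article*

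**What the plan says.** All references are to the Protocol article.

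- **Late entry.** Allocation of patient (text after Fig. 2) says that after the study began "some large dispatch centres still seemed not ready to dispatch the HEMS because of legal uncertainties". Such centres "were excluded until being completely ready to comply with the study protocol". For the same reason "an amendation to extend the study period was filed". The text does not say how many centres were affected, which stations they belong to, when they joined, or whether the extension lengthened the control phase.
- **Order of treatments.** "There are four HEMS stations serving the Netherlands". Because training capacity is limited, "a stepped-wedge design was chosen" (Training of HEMS personnel). Stations work without ECMO first. The same section continues, on the end of training: "After completion, HEMS stations will be equipped with ECPR facilities".
- **Primary test.** Under Statistical analysis, the difference in hospital survival "will be tested using univariate analysis (intention to treat"), by a Chi-square test of intervention against control.
- **Secondary model.** The same section concedes that the unadjusted test may be biased by clustering and plans a GEE for this and for other confounders. Baseline and EMS or dispatch variables may enter. The confounders named are age, gender, ambulance arrival time, low-flow time and cardiovascular conditions, and these enter only if p < 0.2 between the groups.

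**The concern.** In a design that runs control first and ECPR second, a centre's missing early months are control months until its station crosses over. Late entry therefore changes where the patients in each arm come from. It is a change in composition, not a matter of correlated outcomes, so a variance that allows for clustering would not remove it.

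The pooled Chi-square takes no account of dispatch centre, station or calendar period. If late catchments have different survival under the same treatment, part of the observed difference would be a difference between places. The article gives one route by which catchments could differ. Background says that low-flow time lengthens far from an ECPR centre, and Sample size assumes different control survival with and without transport to such a centre.

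**Working it through.** **1. The plan's own figure.** Control survival is 0.30 × 0.26 + 0.70 × 0.16 = 0.19; ECPR survival is 0.35; the planned difference is 16 points. A two-sided 5% comparison of two proportions with 90% power needs 160 per arm (172 with continuity correction). If the 30% assumed for the first 3 months pulls the ECPR rate down to 34.5% or 34.0%, it needs 170 or 180. The stated 175 is therefore reproduced to within 3%. The article used simulation, which cannot be repeated exactly, and does not state sidedness. The values 0.19 and 175 are used below.

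**2. Effect of late entry on a centre's phase mix.** Let a station cross over at fraction x of the study and a centre join at fraction d, with constant accrual. ECPR time is 1 − max(x, d) and control time is max(0, x − d). For d < x the ECPR share is (1 − x)/(1 − d), which rises with d. For d ≥ x it is 100%. As an illustration, assume four equal stations crossing at 20, 40, 60 and 80% of the study:

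| Centre joins at | 1st station | 2nd | 3rd | 4th | All four |
|---|---|---|---|---|---|
| Start | 80% | 60% | 40% | 20% | 50% |
| 10% | 89% | 67% | 44% | 22% | 56% |
| 20% | 100% | 75% | 50% | 25% | 62% |
| 40% | 100% | 100% | 67% | 33% | 75% |

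Against an on-time centre at the same station, the ECPR share can only rise, unless the extension added control time.

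**3. Bias and type I error on assumed shares.** Bias = (late-centre share of ECPR patients − late-centre share of controls) × difference in baseline survival. Assume shares of 30–40% and 10–20%, and a survival difference of 5–10 points.

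- Smallest: (0.30 − 0.20) × 0.05 = 0.005
- Intermediate: (0.30 − 0.10) × 0.05 = 0.010 and (0.40 − 0.20) × 0.10 = 0.020
- Largest: (0.40 − 0.10) × 0.10 = 0.030

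SE = √(2 × 0.19 × 0.81 / 175) = 0.042. With bias b and no treatment effect, type I error = 1 − Φ(1.96 − b/SE) + Φ(−1.96 − b/SE). This gives 5.2%, 5.7%, 7.6% and 11.0% for b = 0.5, 1, 2 and 3 points.

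**4. Cross-check from the schedule in step 2.** Let late centres cover 25–50% of the catchment and join at 10–40% of the study. They then supply 23–50% of ECPR patients and 9–44% of controls. At the upper end (50% of catchment, joining at 40%), summed over stations, late centres have 0.5 × 1.8 = 0.9 units of ECPR time against 0.5 × 2.0 = 1.0 for the others, a share of 0.9/1.9 = 0.47. For control time the share is 0.3/1.3 = 0.23. The gap of 0.243 × 0.10 gives 2.4 points. Across all combinations the bias is 0.2–2.4 points and the type I error 5.0–8.4%, with the variance taken at the mixed survival rates. This counts catchment mix only, without secular trend or clustering.

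**5. How large the survival difference could be.** On the article's figures, moving every control patient in a catchment from no transport to in-hospital ECPR changes survival by 0.26 − 0.16 = 0.10. By this route alone, 10 points is the ceiling, and 5 points needs the transported share to differ between catchments by 0.05/0.10 = 50 percentage points.

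**The case against.** A reader might infer that the late centres contribute mainly ECPR-phase patients and hardly any controls. The document does not show this. It gives no joining dates, and the crossover timetable is in Fig. 3, which was not available for this check. In the illustration, a centre at the last-crossing station that joins at 10–40% of the study still has only 22–33% of its patients in the ECPR phase. The extension was filed because of these centres and may have added control time, which would shrink the imbalance.

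A reader might also infer that large and small centres differ in response times and bystander CPR. No section says so. The Discussion calls the Dutch system homogenous, with full coverage of early CPR. Distance to an ECPR hospital is the one route with support in the text. Eligibility criteria narrow it by excluding patients expected at a ready ECPR centre within 30 minutes, though the article adds that very few patients are that close.

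Third, the plan does not ignore confounding. It admits that the Chi-square may be biased and allows dispatch variables in the GEE. The article may leave the cluster unit and the full covariate list to the full protocol or SAP, so it cannot be said that no analysis will condition on centre.

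These points limit the size and certainty of the bias. They do not remove it from the primary test, which the article fixes as unadjusted and which a secondary model cannot protect.

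**Conclusion.** The point holds in a limited form. Late entry takes control time first, so the late centres are likely under-represented among controls unless the extension restored that time. The primary test would absorb any resulting shift in catchment. On the assumed shares and survival differences the bias is about 0.5–3 points and the type I error about 5.2–11%. The upper end needs the extreme value of all three assumptions together, and the schedule-based check stops at 2.4 points and 8.4%. At the low end the effect is negligible. Against a planned difference of 16 points it would not by itself create or erase the hoped-for effect. Its direction is unknown, because the document does not say whether late catchments have better or worse survival. The change should be made because it is cheap and reaches the primary inference.

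**What to change.** 1. Base the primary inference on a model that conditions on dispatch centre, as fixed strata or as a random intercept nested in station, and on calendar period. A random intercept belongs in a mixed logistic model, which the plan already uses for neurological outcome, and not in a GEE. Station and period alone are not enough, because the mix of centres within a station can change as its treatment changes. Keep the Chi-square as descriptive.
2. Pre-specify a sensitivity analysis restricted to centres that enrolled in both the control and the ECPR phase of their station. Use the same model, since restriction alone does not balance the phases within a centre.
3. Report each centre's joining date and its patients per phase, and state whether the extension added control time.

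The cost is mainly analysis wording. Dispatch centre is not among the variables under Other data collected, so confirm that it can be recovered for every patient. Some precision will be lost; how much is not computed here and should be checked by repeating the sample-size simulation under the new model. Strata may be sparse, with about 175 × (0.19 + 0.35) = 94.5, or 95, expected survivors. The sensitivity analysis loses the patients of late centres that enrolled no controls.
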